#### Low-risk general adolescent cohort

A second cohort of adolescents per slum cluster not at high risk for depression and/or self-harm/suicide will be identified by selecting a random sample from the remaining screened population matched by gender and age per slum. This will form the ‘low-risk’ cohort. The numbers per slum will be in proportion to the high risk per slum by gender and age.

### Exclusion criteria

The following adolescents will not be included in the study.Adolescents with severe physical or mental ill-health that would prevent them from giving consent or participating in the studyAdolescents or their guardians who do not provide informed written consentAdolescents who are temporary residents of the slums such as visiting relatives/friends

The implementation team will comprise of researchers, project staff, and field investigators. Project staff will continuously monitor the trial implementation and support field staff, NPHW and UPHC doctors. Research staff will continuously monitor the data and provide feedback to the field staff about any deviations. In addition, 10% of data will be re-assessed by the designated field staff to ensure quality control, and corrective steps will be taken as needed. They will ensure maximum inclusivity of adolescents who manifest either physical or mental illness and field investigators will be provided training in lines with the adapted Guidelines on Disability Inclusion in Research [48] to ensure that as many adolescents as possible are included in the study.

### Randomisation

Randomisation will be conducted at the level of the slum cluster, in a 1:1 ratio to intervention or control using a central allocation sequence. Natural remission variation between screening and rescreening may be used if deemed appropriate for stratification prior to randomisation. The clusters will be stratified by location, average remission rate for depression between screened and re-screened population per slum cluster and median population of each slum cluster. The slum cluster selected under each intervention and control arms will be non-contiguous to avoid contamination. The random allocation will be performed using a software-based random number generator by a statistician not involved in study conduct or analysis. To maintain blinding, the unblinded statistician will generate the randomisation list and share it directly with field staff. The blinded study statistician as well as the principal investigator will remain blinded until data lock.

### Intervention components

The two core intervention components of the ARTEMIS described above include the community anti-stigma campaign and electronic decision support system. Figure 2 outlines how the different components of the trial work together.

**Fig. 2 Fig2:**
[figure not shown]
Intervention prototype of ARTEMIS study

The anti-stigma campaign will be implemented immediately post-randomisation and will continue throughout the intervention period, which will include different strategies of creating awareness using multimedia approaches, having a social contact approach (where people with lived experiences share their experiences through videos, in-person talks) and delivering these strategies.

### Control arm

The control arm slum cluster will receive usual care (currently the usual care practice involves very little support for mental disorders and only those with severe disorders are referred to a mental health professional) from their UPHC and general psychoeducation through brochures and pamphlets only. As part of good clinical practice, adolescents identified at high risk for depression or self-harm/suicide will be advised to consult a doctor or mental health professional for further diagnosis and treatment. If any adolescent is identified with severe depression, (a score of >=15 on PHQ9) and/or at high risk of suicide (suicide score >=2) during the screening, they and their parents/guardians will be advised to seek professional help immediately. A list of health facilities (with contact details) where such treatment is available will be provided to them. Further, the implementing team will request NPHW to follow up with the adolescent and their families more intensively and recommend them to visit a doctor/psychiatrist immediately. The implementation team will check to see whether the NPHW has made follow-up visits to such adolescents.

### Both arms

For all UPHCs, that fall within the study sites, the implementing team will liaise with government and private pharmacies to ensure the availability of appropriate medications. We will also explore collaborative strategies with the Ministry of Health and Family Welfare of both states (Andhra Pradesh and Delhi), to enhance the availability of common psychotropic medications for adolescents as per the Essential Drugs List in the UPHCs. Detailed contact information will be collected from all participants, such that follow-up can be done. The study participants will be constantly followed up for their wellbeing by the NPHWs and will also provide a great deal of motivation and encouragement to them to seek help for their mental illness on a regular basis.

### Data collection

Independent field investigators, blinded to intervention allocation, will be involved in data collection at each phase of the study. Quantitative data on stigma perceptions related to mental health, depression will be collected prior to randomisation (Time 0) and then subsequently at 3, 6, 12 months of the intervention. All data including clinical data of study participants will be captured on tablets, de-identified and saved in a secure server.*Time - 0 month (pre-randomisation):* The names of those adolescents at high-risk will be shared with trained interviewers who will then administer a detailed questionnaire that will enquire about socio-demographic characteristics, treatment history, history of any mental illness, family history of any mental illness, social support from friends and families, stressful events experienced in the last one year, resilience, history of any co-morbid major physical illnesses.. Questions related to costs incurred on treatment will be directed to the parents/guardians of the adolescents.*Time – 3, 6, and 12 months (intervention phase):* Data will be collected from the study cohort from the intervention arm and the study cohort from the control arm (both low risk and high risk) across all the slum clusters by trained interviewers. Questionnaires administered will be the Patient Health Questionnaire (PHQ9), Knowledge, Attitude, and Behaviour (KAB) scale [49] and Barriers to Access to Care Evaluation- Treatment Stigma (BACE-TS) [50], Connor-Davidson Resilience Scale (CD-RISC - 10) [51] at these time points.

### Tools used for data collection

i)PHQ9—The PHQ9 consists of 9-items. The final score is calculated by assigning scores of 0, 1, 2, and 3, to the response categories of “not at all”, “several days”, “more than half the days”, and “nearly every day”, respectively. PHQ-9 total score for the nine items ranges from 0 to 27, and scores 5–9 indicate mild, 10–14 indicate moderate, 15-19 indicate moderately severe, and 20–27 indicate severe depression. This instrument will provide a reliable estimate of depression in the communities and also the proportion among the screen positive individuals who have accessed mental health services. A cut-off score of ≥5 is indicative of mild depression needing further follow-up and assessment by the NPHWs, whereas a score of ≥10 needs clinical assessment by a PHC doctor.ii)CD-RISC – 10 scale—This scale consists of 10 items measuring resilience. Responses are rated on a 5-point Likert scale, ranging from 0 (not true at all) to 4 (true nearly all the time). Each score has a minimum score of 0 and a maximum score of 4. The total scores are calculated by adding the scores of all 10 items. Higher scores suggest greater resilience and lower scores suggest less resilience, or more difficulty in bouncing back from adversity.iii)KAB scale—KAB is used to measure the knowledge, attitude and behaviour related to mental health, and is a 16-item questionnaire. 12 of the items ascertain mental health knowledge, attitude and behaviours to understanding stigma. It has two subgroups—the behaviour subgroup and the knowledge and attitude subgroup. The behaviour subgroup is based on the Reported and Intended Behaviour Scale which uses a 5-point Likert scale (ranging from ‘agree strongly’ which scored 1, to ‘disagree strongly’ which scored 5). Higher scores suggest increased stigma, except for those questions which had a negative connotation. The knowledge and attitude subgroups were identified based on discussion with experts hence does not have the properties of a scaleiv)BACE – TS scale—This is a 12-item questionnaire with a four-point Likert scale, with scores ranging from 0 to 4, which asks questions on the stigma associated with seeking help for mental illnesses. Higher scores suggest higher stigma.

The SPIRIT 2013 statement, 33-item checklist and figure [52] is being used to schematically represent the study participants’ timeline of enrolment, eligibility screening, allocation, intervention and assessments at four timepoints (please see Fig. 3) and to guide the overall standards of a cRCT.

**Fig. 3 Fig3:**
[figure not shown]
Study participants’ timeline of enrolment, eligibility screening, allocation, intervention and assessments at four timepoints

#### Anti-stigma component (combined high- and low-risk cohorts)

##### Primary outcome

Change in mean behaviour scores of adolescents at 12 months using the KAB scale

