**Methods:**

The intervention will be implemented as a cluster randomised control trial in 30 slum clusters in each of the cities of Vijayawada and New Delhi in India. Adolescents aged 10 to 19 years will be screened for depression and suicide ideation using the Patient Health Questionnaire (PHQ-9). Two evaluation cohorts will be derived—a high-risk cohort with an elevated PHQ-9 score ≥ 10 and/or a positive response (score ≥ 2) to the suicide risk question on the PHQ-9, and a non-high-risk cohort comprising an equal number of adolescents not at elevated risk based on these scores.

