The implementation of the mobile technology-based EDSS will include the following:Trained interviewers will administer the PHQ-9 to adolescents aged 10 to 19 years in the selected slum clusters to screen for depression and suicide/self-harm risk. They will use a tablet-based questionnaire to generate composite scores to identify ‘high-risk’ adolescents.NPHWs and doctors will be trained by the research team before the beginning of the intervention. Training of NPHWs and UHC doctors will be provided by in-person training and via the virtual conferencing platforms developed earlie r[24]. The NPHWs will then provide basic supportive advice such as engaging oneself in hobbies, strengthening social contact, and so on, and a referral to the UPHC doctor. High-risk adolescents will be electronically referred via the mHealth platform and provided with a paper referral card to take to the doctor.The UPHC doctor will then review adolescents at high risk as part of a health camp organised in the slum or examine the patient who may directly visit the UPHC. Data from adolescents at high risk will be uploaded, with their consent, to a secure health record using the Open Medical Record System (MRS) open source, electronic health record system.A decision support application based on WHO’s mhGAP-IG algorithm will be integrated in a tablet device and that will be used by UPHC doctors to diagnose and manage patients experiencing depression, other significant emotional or medically unexplained complaints and or having self-harm/suicide ideation. Doctors will use the depression, other significant emotional or medically unexplained complaints and self-harm/suicide modules of mhGAP-IG, especially related to adolescents. Adolescents at high risk of requiring medication can access these directly from the UPHC or purchase low-cost generic medication from a private pharmacy.For adolescents with complex needs, consultation with a specialist psychiatrist will be available as needed. The psychiatrist will also conduct case reviews via phone and/or video conferencing with the UPHC doctors to enhance their management skills. Alternatively, such adolescents can be referred by the UPHC doctor to a psychiatrist in the next tier of the public health system.NPHWs will conduct follow-up visits and assess treatment adherence using the traffic light system to guide them about the status of each high-risk adolescent catered to by a particular NPHW.

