## Research methods

### Aim

The study aims to test clinical effectiveness and cost-effectiveness of the implementation strategies to identify and reduce depression and suicide risk among adolescents living in urban slums. The study hypothesises that**:**A community-based anti-stigma campaign will lead to significant improvements in community behaviours toward adolescents with depression, other significant emotional or medically unexplained complaints and increased risk of self-harm/suicide; andA mobile device-based decision support system will improve the treatment of adolescents at high risk of depression, other significant emotional or medically unexplained complaints and increased risk of self-harm/suicide and lead to higher remission rates from depression and reduced suicide risk.

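### Both primary contrasts estimate the effect of the combined ARTEMIS package, but the hypotheses and outcome labels credit the campaign and the decision-support system separately

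*Protocol article*

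**What the plan says.** All references are to the Protocol article.

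- **Hypotheses (Aim).** The first reads: "A community-based anti-stigma campaign will lead to significant improvements in community behaviours toward adolescents with depression". The second credits the mobile decision-support system with better treatment, higher remission and lower suicide risk. Developing the intervention makes the same split.
- **Primary outcomes.** The change in behaviour score on the KAB scale at 12 months is listed under "Anti-stigma component (combined high- and low-risk cohorts". Remission at 12 months is listed under an mHealth component, in the high-risk cohort only.
- **Arms.** Slum clusters are allocated "in a 1:1 ratio to intervention or control using a central allocation sequence". No factorial or single-component arm is described. On content: "The two core intervention components of the ARTEMIS described above include the community anti-stigma campaign and electronic decision support system". On timing: "The anti-stigma campaign will be implemented immediately post-randomisation and will continue throughout the intervention period". Control clusters receive usual care and "general psychoeducation through brochures and pamphlets only".
- **Who gets the clinical pathway (mHealth-based EDSS).** "High-risk adolescents will be electronically referred via the mHealth platform and provided with a paper referral card to take to the doctor". Doctor review and follow-up by non-physician health workers (NPHWs) come after that.
- **Cohort sizes (Abstract, Methods).** The second cohort is "a non-high-risk cohort comprising an equal number of adolescents not at elevated risk based on these scores".

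**The concern.** Hypotheses worded by component call for contrasts that separate the components, and a two-arm trial of the package has none. High-risk adolescents in intervention clusters live where the campaign runs and are also offered the decision-support pathway, so a remission difference cannot be assigned to the decision support. The behaviour score has a related problem. Half of the pooled sample is offered the clinical pathway as well as the campaign, so a positive result could come partly or wholly from clinical contact.

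At stake is the conclusion. The Abstract's Discussion says the findings are meant to inform governments about strategies for care. If results are reported under the present hypotheses, each component would be credited with an effect that the trial did not isolate.

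**Working it through.** **1. The plan's own sample size.** Inputs from Statistical considerations: 50% vs 65% remission, 90% power, two-sided 0.05, ICC 0.1, 27 per cluster. Sixty clusters allocated 1:1 give 30 per arm.
- Individually randomised n per arm = (1.960 + 1.2816)² × (0.50×0.50 + 0.65×0.35) / 0.15² = 223.
- Design effect = 1 + 26×0.1 = 3.6. Effective n per arm = 30×27/3.6 = 225.
- Power is 0.903 (0.899 with pooled variance). The stated 90% is reproduced. It is power for the package contrast, and nothing below alters it.

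**2. What each contrast estimates.** Let C be the campaign effect, E the extra effect in high-risk adolescents of the clinical pathway over what control clusters offer, and w the high-risk share of the pooled sample. Take C to be the same in both cohorts for simplicity.
- Remission (high-risk only): campaign and clinical pathway together. No analysis of two arms splits this.
- Behaviour score, pooled: (1 − w)·C + w·(C + E) = C + wE. With equal cohorts, w = 0.5, giving C + 0.5E.
- C = 1, E = 0 gives 1.0. C = 0.5, E = 1 also gives 1.0. The pooled result cannot tell these apart.
- If C = 0, the pooled contrast is still 0.5E (0.4E to 0.6E for an assumed w of 0.4 to 0.6).

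**3. What the low-risk cohort adds.** With no spill-over, the low-risk contrast is C. With an assumed spill-over fraction s it is C + sE. If C = 0, that is 0.1E at s = 0.1 and 0.25E at s = 0.25, against 0.55E and 0.625E pooled. It is closer to the campaign effect but not clean.

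**4. Price in precision.** Evaluable per cluster after 20% loss: 33×0.8 = 26.4 low-risk (equal cohort sizes) and 52.8 pooled. Effective n per arm = 30m/(1 + (m − 1)·ICC). Detectable effect at 90% power = 3.2415×√(2/effective n), in SD units. The protocol gives no ICC for the behaviour score, so the ICCs are assumptions.

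| Assumed ICC | Pooled, m = 52.8 | Low-risk only, m = 26.4 | Ratio |
|---|---|---|---|
| 0.02 | 0.164 | 0.200 | 1.22 |
| 0.05 | 0.218 | 0.245 | 1.12 |
| 0.10 | 0.286 | 0.306 | 1.07 |

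Example at ICC 0.05, low-risk: design effect 1 + 25.4×0.05 = 2.27; effective n = 792/2.27 = 348.9; 3.2415×√(2/348.9) = 0.245. The planned adjustment for baseline score is ignored here and would lower all of these figures.

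**The case against.** **The package reading is already in the document.** The Abstract's Background states the hypothesis jointly, Developing the intervention speaks of a complex intervention, and Potential contributions to the field refers to the effect of a combination. This is true, and it shows that the right wording is at hand. It does not cure the Aim or the outcome labels, which say something different.

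**The pooled test is valid.** This stands. It is a randomised comparison of package with control, and no test or sample size is wrong.

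**Analysis by cohort belongs to the analysis plan.** This stands in part. That plan is not shown and may contain it. Statistical considerations also names a subgroup by baseline depression severity, which is close to cohort, though not explicitly for the behaviour score. No analysis plan, however, can split the remission contrast, and a subgroup analysis leaves the meaning of the pooled primary outcome unchanged.

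**The low-risk contrast is not purely the campaign.** This stands. Tools used for data collection calls for NPHW follow-up at PHQ-9 of 5 or more, and the low-risk cohort can include scores of 5 to 9. NPHWs trained for the clinical pathway also distribute campaign materials.

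**Stronger readings to avoid.**
- *The design holds no information on the campaign, or the plan throws it away.* Both cohorts are measured in both arms at 3, 6 and 12 months, so the low-risk contrast can be computed. Only the headline estimate pools.
- *Reweighting to the assumed 3% prevalence would give a community effect.* Low-risk adolescents are matched to the high-risk cohort by gender and age within slum, so weighting by cohort alone does not restore the community. The 3% is also a planning assumption.
- *The campaign is likely to be falsely proved.* Suppose C = 0 and E = 0.30 SD, giving a pooled shift of 0.15 SD. Power is then 0.84, 0.61 or 0.40 at ICC 0.02, 0.05 or 0.10. The effect sizes and the ICCs for this score are all assumed, and nothing in the protocol shows that clinical contact moves it. E may be small, since high-risk controls are also advised to seek care.

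**Conclusion.** The point holds as a mismatch between the stated hypotheses and what the design estimates. Each primary contrast is a valid estimate of the combined package and neither tests one component. For remission this cannot be repaired by analysis. For the behaviour score, the pooled estimate is about C + 0.5E, assuming equal cohorts and a campaign effect common to both; the size of E is unknown. A low-risk contrast comes nearer to the campaign effect, subject to spill-over. The difference between cohorts should not be read as the decision-support effect, because the campaign itself may work differently in high-risk adolescents.

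The Aim's reference to community behaviours also goes further than the outcome, which is the score of sampled adolescents. The outcome definition already says so; the hypothesis does not.

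**What to change.** 1. Restate both hypotheses, and all conclusions on remission and on the pooled behaviour score, as effects of the combined ARTEMIS package, in line with the Abstract's Background and Potential contributions to the field. Relabel the two outcome headings to match.
2. Keep the pooled behaviour analysis as primary. Prespecify cohort and cohort-by-arm terms, if the analysis plan does not already have them, and report the low-risk and high-risk effects separately. Describe the low-risk effect as the closest available estimate of the campaign effect, subject to spill-over and to NPHW follow-up at PHQ-9 of 5 or more. Describe the high-risk effect as the package effect.
3. Describe the result as the behaviour scores of the sampled adolescents, not as community behaviours.

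This costs wording and two model terms, on data already planned for collection. The downside is that effects by cohort are less precise: the detectable difference for low-risk only is 7% to 22% larger than for the pooled sample over the assumed ICCs. Recruitment and sample size do not change.

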##### Secondary outcomes

Change in mean knowledge and attitude scores and change in stigma perceptions of adolescents as assessed by Barriers to Access to Care Evaluation- Treatment Stigma (BACE – TS) Subscale. Change in attitude of parents demonstrated through qualitative interviews of parents selected through purposive sampling will also be captured. The qualitative tool development, data collection and analysis will be done by The George Institute’s qualitative researcher.Change from baseline in mean stigma scores of adolescents

#### mHealth component (high-risk cohort)

##### Primary outcome

Proportion achieving remission (defined as PHQ-9 <5, and/or suicide risk score <2) at 12 months.

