### Eligible population

#### High-risk cohort

All consenting adolescents aged 10 to 19 years will be eligible for screening for depression, or suicide/self-harm risk. The screening will help to identify both high-risk and non-high-risk cohorts. High risk is defined as presence of at least one of the two conditions:High risk of depression based on PHQ-9 score ≥10.Positive response (score ≥2) to the suicide risk question on the PHQ-9.

Field investigators will continue screening until they have identified about 990 adolescents per location at high risk of depression or self-harm/suicide. This will form the ‘high-risk’ cohort. Because there will be some delay (up to 12 weeks) between screening and randomisation the high-risk adolescents will be rescreened to assess if they still meet the inclusion criteria prior to randomisation as literature suggests that around 25% of individuals initially identified at high risk will no longer meet the high-risk criteria at three months [47]. Only those adolescents who continue to remain at high risk during re-screening will form part of the high-risk cohort.

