### Statistical considerations

For high-risk adolescents, assuming a 50% remission rate in the control arm at 12 months based on published data [53], and 30 slum clusters per intervention location, at least 27 subjects per slum cluster are needed to detect a 15% absolute improvement in the intervention arm (65% intervention vs 50% control) at 12 months with 90% power. This assumes a 2-sided significance level of 0.05 and an intra-class correlation coefficient (ICC) of 0.1 based on pilot data [25]. To account for up to 20% of participants lost to follow-up, we will aim to enrol at least 33 participants per slum cluster for a total sample size of 1980 adolescents (60 clusters × 33 adolescents). Assuming a prevalence of 3% of adolescents with depression or increased risk of self-harm/suicide (48), we will therefore aim to screen about 1100 adolescents in each slum cluster. Further assuming that 5% of eligible adolescents will refuse to participate, we aim to screen 1160 adolescents in each slum cluster i.e. a total of 69,600 adolescents (60 slum clusters × 1160 adolescents).

Primary analyses will be conducted at the participant level using either random-effect generalised linear mixed models or generalised estimating equations adjusted for clustering. For the primary outcome, remission at 12 months differences will be assessed using a log-binomial (log link function) or logistic regression (log link function) including a random cluster effect. If using generalised estimating equations, the effect of clustering will be accounted for using a repeated cluster effect with a compound-symmetry variance-covariance structure. The intervention effect will be estimated as odds ratio and corresponding 95% confidence interval.

Sub-group analyses will be conducted according to UPHC-level characteristics (size, location and health service characteristics) and patient-level characteristics (demographic factors and clinical factors e.g. depression severity at baseline). The primary outcome will be assessed at 12 months (and reported as secondary outcomes at 3 and 6 months).

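### The primary remission endpoint joins its two limbs with 'and/or'; read literally, it counts some high-risk participants as in remission at entry, which weakens the planned comparison

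*Protocol article*

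**What the plan says.** All references are to the protocol article.

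- **Endpoint** (mHealth component, Primary outcome): "Proportion achieving remission (defined as PHQ-9 <5, and/or suicide risk score <2) at 12 months".
- **Entry** (Eligible population, High-risk cohort): "High risk is defined as presence of at least one of the two conditions". The two conditions are "High risk of depression based on PHQ-9 score ≥10" and "Positive response (score ≥2) to the suicide risk question on the PHQ-9". Eligibility is confirmed shortly before randomisation: "Only those adolescents who continue to remain at high risk during re-screening will form part of the high-risk cohort".
- **Scale** (Tools used for data collection): "PHQ-9 total score for the nine items ranges from 0 to 27", with each item scored 0 to 3 and totals of 20 or more labelled severe.
- **Planning rates** (Statistical considerations): the sample size is set by "assuming a 50% remission rate in the control arm at 12 months based on published data" and is meant to "detect a 15% absolute improvement in the intervention arm (65% intervention vs 50% control) at 12 months with 90% power".

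No section says whether *and* or *or* governs the endpoint, or links remission to the criterion on which a participant entered. The planning rates are not tied to any one reading.

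**The concern.** An entry rule satisfied by either of two conditions is properly reversed by an exit rule that requires both to be absent. The endpoint does not say this. Its literal sense is that either limb is enough.

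On that reading the endpoint overlaps with eligibility. Some participants are remitted before the intervention starts, whatever their depression score. They raise the remission rate in both arms and leave fewer participants in whom a difference can appear. This is the primary outcome of the mHealth component and the basis of the sample size, so both the estimate and the stated 90% power depend on how one connector is read.

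**Working it through.** **1. Logic of the two rules.** Let T be the PHQ-9 total and S the suicide item. Entry: T ≥ 10 or S ≥ 2. Literal endpoint: T < 5 or S < 2.

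| Participant at entry | Eligible | Remitted, *or* reading | Remitted, *and* reading |
|---|---|---|---|
| T ≥ 10, S = 0 or 1 | yes | **yes** | no |
| T < 5, S ≥ 2 | yes | **yes** | no |
| T ≥ 5, S ≥ 2 | yes | no | no |

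In the first row T can reach 8 × 3 + 1 = 25, which lies in the protocol's severe band. On the *and* reading no eligible participant is in remission at entry.

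**2. The plan's own figure.** Inputs from Statistical considerations and Randomisation: 50% vs 65%, two-sided 0.05, ICC 0.1, 27 evaluable per cluster, 60 clusters allocated 1:1, so 30 per arm over both cities.

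- Individually randomised size, unpooled variance: (1.960 + 1.282)² × (0.50×0.50 + 0.65×0.35) / 0.15² = 223 per arm (pooled variance: 227).
- Cluster size: solve 30m / [1 + 0.1(m − 1)] = n, so m = 0.9n / (30 − 0.1n). This gives 26.1 for n = 223, rounded up to 27 (28.0 for n = 227).
- Power at m = 27: design effect 1 + 26 × 0.1 = 3.6; effective n = 30 × 27 / 3.6 = 225 per arm; power 89.9% (pooled) or 90.3% (unpooled).

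The stated 27 per cluster and 90% power reproduce.

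**3. Illustration of the *or* reading.** Let q be the share meeting the remission definition at baseline (rows 1 and 2 above) and s the share of these who still meet it at 12 months. The documents give neither, so both are assumed. The remaining 1 − q keep the planned 50% vs 65%:

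- control rate = q·s + (1 − q)·0.50
- intervention rate = q·s + (1 − q)·0.65
- difference = 0.15·(1 − q)

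With d the difference, p₀ and p₁ the two rates, p̄ their mean and n = 225, power = Φ{[d√n − 1.96√(2p̄(1 − p̄))] / √(p₀(1 − p₀) + p₁(1 − p₁))}.

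| q | s = 1.00 | s = 0.95 | s = 0.90 |
|---|---|---|---|
| 0.2 | 60.0 vs 72.0%, power 77% | 59.0 vs 71.0%, 76% | 58.0 vs 70.0%, 76% |
| 0.5 | 75.0 vs 82.5%, 49% | 72.5 vs 80.0%, 46% | 70.0 vs 77.5%, 44% |
| 0.7 | 85.0 vs 89.5%, 30% | 81.5 vs 86.0%, 25% | 78.0 vs 82.5%, 22% |
| 0.9 | 95.0 vs 96.5%, 12% | 90.5 vs 92.0%, 8% | 86.0 vs 87.5%, 7% |

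Example, q = 0.5 and s = 0.95: control 0.475 + 0.250 = 0.725; intervention 0.475 + 0.325 = 0.800; power 46%.

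**4. Sensitivity to the effect model.** Step 3 gives the intervention no effect among those already qualifying. If instead the planned failure ratio of 0.35 / 0.50 = 0.70 applied to everyone, q = 0.5 and s = 0.95 would give 72.5% vs 80.7% and power of 54% rather than 46%. The loss is smaller but remains.

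**5. When is a 15-point gain impossible?** Only if the control rate exceeds 85%, that is q > 0.35 / (s − 0.50): 0.70 for s = 1.00, 0.78 for s = 0.95 and 0.875 for s = 0.90.

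**The case against.** The sponsor may well have meant *and*, or a third reading: remission on whichever criterion, or both, the participant entered with. The abstract uses the same connector for the entry rule, so the endpoint may simply mirror it. On either of these readings nobody is remitted at entry. This is a fair account of possible intent, but the article states neither reading. The third would also still count as remitted someone who entered on PHQ-9 alone and has a total below 5 with a suicide item of 2 at 12 months, although that person again meets the high-risk rule.

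It can also be said that the definition could be settled in the analysis plan, without sight of results by arm. The Randomisation section keeps the study statistician blinded until data lock. Statistical considerations has the plan written before unblinding and programs tested on scrambled groups. That largely stands: under the stated procedure, a choice steered by arm-level results is not to be expected. A choice made after seeing pooled data is not excluded. The matters the article leaves to that plan (sensitivity analyses, covariates, secondary endpoints, missing data) do not include the definition of the primary endpoint, which the article itself fixes.

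Two stronger inferences are tempting, and the documents support neither. A reader might infer that most of the cohort is in remission at baseline; no split by entry criterion is given, so the share is unknown. A reader might also infer that the trial cannot show its planned effect; step 5 shows that a 15-point gain is ruled out only at a high baseline share, and at 20% the illustrated power is still about 76–77%.

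**Conclusion.** The concern holds in this form: the primary mHealth endpoint is wrong as written. Its literal reading overlaps with the entry rule in two identifiable groups, and nothing elsewhere in the article resolves it. That part is logic and needs no assumption.

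The size is conditional. On the *or* reading, power falls from 90% to about 76–77%, 44–49%, 22–30% or 7–12% if 20%, 50%, 70% or 90% qualify at baseline. These figures assume that 90–100% of them still qualify at 12 months, that 50% vs 65% applies to the rest, and that the ICC stays at 0.1 with 27 evaluable in each of 30 clusters per arm. They are scenarios, not estimates of this trial's power. On the *and* reading, power stays near 90%, provided the 50% and 65% rates belong to that definition, which the article does not say. The point should be corrected before outcome data are examined.

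**What to change.** - Before any outcome data are examined, replace the connector with one explicit rule under which no eligible participant is in remission at entry. PHQ-9 below 5 *and* suicide risk score below 2 at 12 months does this. It also agrees with the aims (Developing the intervention; Aim), which seek both recovery from depression and lower suicide risk.
- Report the two limbs separately as secondary outcomes.
- Confirm that the 50% and 65% planning rates refer to the chosen definition. If they do not, restate the power.

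**Cost.** A wording change in the protocol, registry entry and analysis plan. No new data are needed, because the PHQ-9, including its suicide item, is already collected at 12 months. If the planning rates came from a different definition, the sample-size calculation must be redone as well.
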